**Fig 2 pone.0321811.g002:**
[figure not shown]
Study Design.

**Fig 3 pone.0321811.g003:**
[figure not shown]
Flow Chart.

#### Statistical analysis.

Statistical analysis will be performed with IBM-SPSS Statistics software version 25 or later. Quantitative variables will be described as mean and standard deviation (SD) if the variable follows a normal distribution or as median and interquartile range for non-normal data. For categorical data absolute and relative frequencies will be computed. The Kolmogorov-Smirnov test will be used to determine the normality of the data. Intra-group variables will be measured with the T-Student test for related samples or the paired samples Wilcoxon test for non-parametric alternative. For inter-group comparations non-parametric analysis will be performed when a non-normal distribution is assumed, using the U Mann Whiney test for comparisons between groups and T-Student test for normal data. Dichotomous variables will be analyzed using the chi-square test. A significant level of 95% will be assumed (p <0.05). If there are more than 15% dropouts, an intention-to treat (ITT) analysis will be performed. Effect size will be calculated using Cohen’s d to determine clinical significance: negligible, small, medium and large differences will be reflected in effect sizes of < 0.2, 0.2–0.5, 0.6–0.8 and > 0.8, respectively.

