### Allocation and blinding

The randomization list will be conducted by the Contract Research Organization (CRO) in a stratified randomization stratified by age and sex using the EPIDAT4 program, a validated system that automates the randomization of treatment arms at the specified ratio, in this case in a 1:1 ratio (NG) or (PG). After baseline the data collection logbook (DCL) will assign a code according to these randomization criteria, which will correspond to the number of the supplementation batch to receive: Nutritional supplement or Placebo.

The treatment will be administered in a double-blind procedure. The allocation list will be kept by specific non-blind personnel from the CRO and the Promoter’s Quality Assurance Department, following good clinical practices. The assessors, the physiotherapist (intervention manager) and other investigators involved in the intervention will be blinded.

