### Procedure

Patients who meet the criteria will be scheduled at their participating center. After signing the informed consent (IC) they will carry out the initial assessment.

At the baseline assessment, the nursing team will conduct a series of evaluations. Blood tests will be performed on all participants, and their oxygen saturation and respiratory rate will be measured. Participants will then complete six scales in a single room, a process expected to take approximately 30 minutes. Following this, they will proceed to the physiotherapy assessment, which will begin with the measurement of Maximum Inspiratory and Expiratory Pressure (MIP/MEP). Next, strength tests will be conducted, including the 30-second Arm Curl Test (30“ACT) and the 30-second Sit-to-Stand Test (30”STST). After a 10-minute rest period participants will undergo the 6-Minute Walk Test (6MWT) to assess aerobic capacity. This test will be conducted according to SEPAR guidelines in a 30-meter corridor [20].

In the final phase of the assessment, a physiotherapist will explain the prescribed exercise regimen tailored to each participant’s level and will also install the telerehabilitation mobile application (HEFORA) on the participant’s device.

After randomization by the computer system, the nursing team will provide each participant with a supplement (Nutritional supplement or Placebo). The entire evaluation process will be repeated at the last visit, scheduled for day 84 ± 4, following the same procedures (Fig 2).

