#### Sample size calculation.

To estimate the sample size, a hypothesis test comparing the proportions of independent groups (PG vs. NG) assuming an alpha risk of 0.05 and a beta risk of 0.2 in a bilateral contrast requires 110 subjects in the placebo group and 110 subjects in the Nutritional supplement group to detect the difference in percentage of patients that will improve their EQ-5D-5L after intervention between the two groups, expected to be 30% and 50%, respectively, as statistically significant, and including a 15% loss estimated. Likewise, to assess the improvement in the pro inflammatory balance considering in this case the proportion of patients with change between pre-post intervention balances in each of the groups the estimated sample size will allow a difference of 20% or more between the two to be declared statistically significant, with a confidence level of 95% and a power of 80%. The estimation was carried out using the GRANMO sample size calculator, version 7.12 (Fig 3).

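### Continuous outcomes are compared between arms by an unadjusted test that a normality check selects, so measured baselines and randomisation strata go unused and precision is lost

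*Protocol article*

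**What the plan says.** The protocol article's Statistical analysis section names the between-arm tests outright. On the choice of test it says: "The Kolmogorov-Smirnov test will be used to determine the normality of the data". Depending on the result, continuous variables are compared between arms "using the U Mann Whiney test for comparisons between groups and T-Student test for normal data". Dichotomous variables get a chi-square test. The article names no regression, covariate-adjusted or stratified analysis.

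Two features of the design bear on this:

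- Under Allocation and blinding, patients are randomised 1:1 "in a stratified randomization stratified by age and sex using the EPIDAT4 program".
- Under Procedure, baseline is measured and then "The entire evaluation process will be repeated at the last visit, scheduled for day 84 ± 4". Each assessed outcome therefore has a baseline value and a day-84 value.

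The primary outcome section analyses EQ-5D-5L in two forms: as a continuous variable, with statistics that depend on its distribution, and as the percentage of patients who improve. The sample size rests on the second form. The test menu above applies to the first form and to the continuous secondary outcomes.

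**The concern.** There are three weaknesses, of unequal weight.

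1. **Baseline is not a covariate.** A patient's starting score usually predicts the final score. A test that leaves it out treats that predictable variation as noise.
2. **The strata are not in the analysis.** Stratified allocation balances age and sex between arms, but an unadjusted test on final values still counts their variation as error. Its standard error is then somewhat too wide for the design.
3. **The data choose the contrast.** Student's t compares means; Mann-Whitney compares ranks. The normality result therefore decides which question the continuous comparison answers, and Mann-Whitney alone gives no difference in EQ-5D units. The planned Cohen's d is a standardised mean difference, so it does not match a rank test.

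At stake are the precision of the continuous EQ-5D-5L comparison and of the continuous secondary outcomes, and clarity about what the continuous comparison estimates.

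**Working it through.** **Step 1. The plan's own sample size.** Inputs from the Sample size calculation section: "assuming an alpha risk of 0.05 and a beta risk of 0.2 in a bilateral contrast"; proportions "expected to be 30% and 50%, respectively, as statistically significant, and including a 15% loss estimated".

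With the pooled-variance formula and no continuity correction, the mean proportion is 0.40 and

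n = [1.960 × √(2 × 0.40 × 0.60) + 0.8416 × √(0.30 × 0.70 + 0.50 × 0.50)]² / 0.20² = 3.720 / 0.04 = 93 per arm.

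Allowing for 15% loss, 93 / 0.85 = 109.4, which rounds up to 110. This matches the stated figure exactly: the plan "requires 110 subjects in the placebo group and 110 subjects in the Nutritional supplement group". The unadjusted chi-square comparison is therefore correctly sized.

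**Step 2. Power for a continuous outcome.** Inputs:

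- 93 evaluable per arm, from Step 1.
- Two-sided alpha of 0.05, from the document.
- Effect of 0.4 SD of the final value: **assumed**, not in the document.
- Correlation r between baseline and day 84: **assumed** 0.4 to 0.7, not in the document. Equal SDs at both times are also assumed.

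The SD that drives the test, relative to the SD of the final value, is:

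- final values: 1
- change scores: √(2(1 − r))
- ANCOVA on baseline: √(1 − r²)

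The noncentrality is (0.4 / relative SD) × √(93/2). For final values this is 0.4 × 6.819 = 2.728. For ANCOVA at r = 0.5 it is 2.728 / 0.866 = 3.150. Power follows from the noncentral t distribution with 184 degrees of freedom:

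| r | Final values | Change scores | ANCOVA |
|---|---|---|---|
| 0.4 | 77.4% | 69.7% | 84.1% |
| 0.5 | 77.4% | 77.4% | 88.0% |
| 0.6 | 77.4% | 85.9% | 92.4% |
| 0.7 | 77.4% | 93.9% | 96.7% |

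The variance of ANCOVA is 1 − r² of that for final values, and (1 + r)/2 of that for change scores. It is therefore smaller than the first for any r other than 0, and smaller than the second for any r below 1. Below r = 0.5, change scores do worse than final values.

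**Step 3. The same gain in patients.** With 93 per arm, the final-value test has 80% power at 0.411 SD. For 80% power at that effect, ANCOVA needs 85 evaluable per arm at r = 0.3, 70 at r = 0.5 and 48 at r = 0.7.

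**Step 4. The strata.** Simulation: 6,000 trials per setting, 92 per arm, four balanced strata assumed to explain 5 to 10% of outcome variance. The unadjusted t test on final values had type I error of about 3.7 to 4.8%, against a nominal 5%. Adjusting for the strata alone added about 1 to 3 points of power.

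**Step 5. The normality check.** Simulation: 3,000 trials per shape, 93 per arm. The two-stage procedure kept type I error at 4.7 to 5.6%. With the two skewed shapes tried, the check sent 98% and 100% of trials to Mann-Whitney; with normal data, about 8%. Those shapes are assumed and are not EQ-5D-5L data.

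**The case against.** The strongest reply is that this is a preference for efficiency and not an error. Randomisation makes the stated tests valid, 110 per arm is right for the comparison that was sized, and covariate adjustment is often set out in an analysis plan that is not shown here. The first two points stand. The third stands only in part: the article does not leave the tests open but names them, so the comment is about a stated method.

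Three stronger readings are tempting, and the documents do not support them.

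- *The estimand of the main comparison is unknown until the data are seen.* The sized comparison is the percentage improved, tested by chi-square. No normality check applies to it, and its contrast is fixed. The objection reaches only the continuous form of EQ-5D-5L and the other continuous outcomes.
- *The plan ignores baseline.* Improvement is defined against the baseline score, and the Statistical analysis section does not say whether arms are compared on final or change values. If change scores are used, baseline does enter. What can be said is that baseline is not a covariate and that ANCOVA is more efficient than either alternative.
- *The strata or the normality check make the tests invalid.* Leaving out the strata makes the final-value test slightly conservative, and the normality check left type I error close to nominal.

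The size of the gain also depends on an r the document does not give. At r = 0.7, ANCOVA beats change scores by only about 3 points (96.7% against 93.9%).

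**Conclusion.** The point holds for continuous outcomes, as a free improvement to a stated method. The trial is not underpowered under its own plan. Under the assumed 0.4 SD effect, 93 evaluable per arm and r from 0.4 to 0.7, ANCOVA gains about 7 to 19 points of power over final values (84.1 − 77.4 to 96.7 − 77.4) and about 14 down to 3 points over change scores (84.1 − 69.7 to 96.7 − 93.9). The direction does not depend on r within this range; the size does. Most of the gain comes from baseline and little from age and sex.

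The harm of the normality check is that the continuous contrast is not fixed in advance, not that it inflates error. No loss has been computed for the percent-improved comparison, so adjusting it is a secondary suggestion. This should be changed, but it does not invalidate the trial.

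**What to change.** Before unblinding:

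1. Drop the Kolmogorov-Smirnov check as the way to choose the between-arm test.
2. For continuous outcomes, including continuous EQ-5D-5L, prespecify one model: ANCOVA of the day-84 value on arm, baseline value, age and sex. Report the adjusted mean difference in the outcome's own units, with robust or bootstrap intervals for skewed scores.
3. As a secondary step, adjust the percent-improved comparison for baseline, age and sex by logistic regression, and report the result as a risk difference.

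The covariates are already collected and no extra patients are needed. The cost is slightly more analysis work and a dated amendment made while blinded. The date matters because the Study design section projects the end of data collection for April 2025, and step 3 changes the analysis of the sized endpoint.

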### Eligibility criteria

All potential participants will be informed before and will have to give their written consent to participate in the study. The inclusion criteria will be: 1) Aged 18–70 years; 2) Diagnostic criteria for having had COVID-19; 3) PCC symptoms for more than 12 weeks, from the end of the acute phase; 4) Fatigue >4 points on the Fatigue Severity Scale (FSS); 5) Independent locomotion. The exclusion criteria will be: 1) Neurological disease preventing them from following the program; 2) Respiratory failure: SaO2 < 90% or respiratory rate ≧30; 3) Rheumatic diseases or acute musculoskeletal injuries that contraindicates exercise; 4) Not daily access to the Internet; 5) Unable to follow oral and written instructions in Spanish; 6) Allergies to fish, shellfish, crustaceans or any of the components of the supplement; 7) Patients who have participated in or completed another clinical trial for the treatment of symptoms derived from COVID-19 in the last 4 weeks; 8) To take immunosuppressive drugs, corticosteroids or non-steroidal anti-inflammatory drugs in the last 2 weeks and 9) Being pregnant. The dropout criteria will be: 1) Pregnancy; 2) At the discretion of the researcher for safety reasons, and/or an adverse event; 3) Non-compliance or lack of adherence to the protocol for more than 2 consecutive weeks.

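### Intention-to-treat analysis is tied to an observed dropout rate above 15%, the same loss the sample size allows for, so the analysis set is left to the data

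*Protocol article*

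**What the plan says.** One sentence in the protocol article, under Statistical analysis, deals with the analysis population: "If there are more than 15% dropouts, an intention-to treat (ITT) analysis will be performed". No other section makes ITT unconditional, and none names the set to be analysed at or below 15%.

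Three other places bear on it:

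- **Sample size calculation.** The target of 110 per arm is stated as "including a 15% loss estimated", so the planned loss and the ITT threshold are the same figure.
- **Eligibility criteria.** The dropout criteria include "Non-compliance or lack of adherence to the protocol for more than 2 consecutive weeks", as well as withdrawal at the researcher's discretion for safety or an adverse event, and pregnancy. All of these can arise after randomisation.
- **Procedure.** The only post-baseline assessment of the primary outcome is the final visit at day 84 ± 4. The article does not say whether withdrawn patients attend it.

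**The concern.** Randomisation protects the comparison of all patients as randomised. It does not protect a comparison of those who remain once patients have been removed for events after randomisation. Here the protected analysis is promised only if an observed rate crosses a threshold, and one patient more or fewer near that threshold decides whether it is done.

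The removals are not neutral by construction. The arms take different products (a fish-oil fraction and refined olive oil, Nutritional Intervention section), so tolerability and adherence could differ between them. If those who leave one arm differ in prognosis from those who leave the other, the between-arm difference in the primary endpoint is distorted.

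The rule is written into the article. A fuller analysis plan could add detail, but an unconditional ITT there would contradict this sentence and the two would have to be reconciled.

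**Working it through.** **1. The plan's sample size.** Inputs from Sample size calculation: two-sided alpha 0.05, power 0.80, 30% versus 50% improving, 15% loss. With the pooled-variance formula and no continuity correction:

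n = [1.960·√(2·0.40·0.60) + 0.842·√(0.30·0.70 + 0.50·0.50)]² / 0.20² = 93 per arm; 93 / (1 − 0.15) = 109.4, rounded up to 110.

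This reproduces the stated 110 per arm. The sample size is not in error.

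**2. Where the trigger sits.** 0.15 × 220 = 33. More than 15% therefore means 34 or more.

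**3. How often ITT would be triggered.** P(X ≥ 34) for X ~ Binomial(220, p):

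| True dropout rate p | P(ITT triggered) |
|---|---|
| 10% | 0.7% |
| 12% | 7% |
| 15% | 45% |
| 18% | 86% |
| 20% | 96.5% |

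At the planned rate, whether ITT is run is close to a coin toss.

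**4. What informative dropout could do to a comparison of completers.** The documents give no dropout rate by arm and no outcome rate among dropouts, so these are assumed scenarios: no true effect, the same base rate of improvement in both arms, 15% lost per arm (110 × 0.85 = 93.5, taken as 94 completers) and placebo dropouts at random. The type I error comes from exact binomial enumeration of the pooled chi-square test at a nominal 5%.

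| Base rate | Supplement-arm dropouts | Supplement completers | Spurious difference | Type I error |
|---|---|---|---|---|
| 40% | all non-improvers | 0.40/0.85 = 47.1% | +7.1 points | 15.9% |
| 30% | all non-improvers | 0.30/0.85 = 35.3% | +5.3 points | 12.2% |
| 40% | improve at half the base rate | (0.40 − 0.15·0.20)/0.85 = 43.5% | +3.5 points | 7.4% |
| 30% | improve at half the base rate | (0.30 − 0.15·0.15)/0.85 = 32.6% | +2.6 points | 6.8% |

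When dropout is equally informative in both arms, the same enumeration gives 4.7% to 5.1%, that is, no inflation.

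**5. Does imputation alone cure this?** In the two all-non-improver scenarios, multiple imputation by arm was simulated with covariates that carry no information on the missing outcome. The spurious difference stays at about +7 points (base 40%) and +5 points (base 30%), with type I error of about 17% and 12–13%. The distortion comes from outcomes missing not at random, and by-arm imputation alone does not remove it.

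**6. Power under an unconditional all-randomised analysis.** With outcomes on all 110 per arm, power for 30% versus 50% is 86.2%. Suppose 15% are lost at random in each arm and counted as non-improvers (an assumption; the article names no rule). The rates become 0.30 × 0.85 = 25.5% and 0.50 × 0.85 = 42.5%. Power at 110 per arm is then 76.2% by the normal approximation and 76.8% by exact enumeration; 121 per arm would restore 80%.

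**The case against.** The strongest counter-argument is that the harm of the trigger itself cannot be measured from the document. The type I error figures come from informative missing outcomes, which would trouble an ITT analysis too if those outcomes were never collected. What an all-randomised analysis adds directly is the withdrawn patients who still have a day-84 value, and the article does not say how many that would be. This stands: a reader might infer that the trigger costs 16% against 5% type I error, and the documents do not support that.

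There are also reasons to expect similar dropout in the two arms: double-blind treatment, a matching placebo with equal posology, and the same exercise programme. This stands as a reason to call the one-sided scenarios illustrative. It does not exclude arm-related withdrawal, because blinding does not stop a product from being tolerated differently.

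Two further readings go too far. One is that the plan expects no ITT. The 15% is a planning allowance, and at a true 15% rate ITT would still be triggered in about 45% of trials. The other is that the article prescribes a completer analysis. It names no set below the threshold, and it does not say whether the triggered ITT replaces or supplements that set. Exclusion of dropouts is an inference, though a strong one: if all randomised patients were already the default, the sentence would have no purpose.

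Finally, the details of an imputation model may properly be left to an analysis plan that is not shown. That does not excuse the trigger, which the article itself states.

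**Conclusion.** The point holds as a badly fixed rule. Whether an ITT analysis is done depends on an observed dropout count, with the cut between 33 and 34 of 220 at the plan's own loss allowance. At or below the cut, the implied set omits patients withdrawn after randomisation for reasons that can depend on arm, so the between-arm comparison can be biased.

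The direction and size of that bias are unknown. The 7–16% type I error range rests on assumed 15% loss per arm, base rates of 30–40% and informative dropout in one arm only. It shows what arm-specific informative missingness could do, not what deleting the trigger would gain. The 45% figure assumes a true dropout rate of 15% and independent dropouts.

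**What to change.** Before unblinding, delete the 15% condition. State that the primary analysis includes every randomised participant in the assigned arm, whatever the dropout rate or adherence, and uses day-84 EQ-5D-5L from withdrawn patients where it is available.

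State a method for missing outcomes. Because imputation by arm would not by itself remove arm-specific informative missingness, add a sensitivity analysis in which dropouts do worse, by amounts that differ between the arms. Label completer and per-protocol analyses as supportive.

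The cost is a change of wording, a little more analysis and possibly some dilution of the estimate. The stated 110 per arm can stay. If dropouts were counted as non-improvers, power would be about 76–77% rather than 80%.

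### Cohen's d, the only effect measure named and the criterion of clinical significance, fits neither the percentage endpoint that sizes the trial nor the rank-tested variables

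*Protocol article*

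**What the plan says.** Under Statistical analysis, the protocol article sets three between-group tests by data type. Normal quantitative variables get Student's t. Non-normal ones get Mann-Whitney and are described by "median and interquartile range for non-normal data". For binary data: "Dichotomous variables will be analyzed using the chi-square test". Categorical data are described by counts and percentages.

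The section then names one effect measure: "Effect size will be calculated using Cohen’s d to determine clinical significance". It attaches four labels to d: negligible below 0.2, small from 0.2 to 0.5, medium from 0.6 to 0.8, and large above 0.8. The sentence is not restricted to any type of variable.

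The Sample size calculation section sizes the trial "to detect the difference in percentage of patients that will improve their EQ-5D-5L after intervention between the two groups", with rates "expected to be 30% and 50%, respectively, as statistically significant". It justifies the comparison of pro-inflammatory balance as a proportion too. The primary outcome section analyses EQ-5D-5L in two forms: as a continuous score and as the percentage who improve.

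**The concern.** The rule gives one measure for three kinds of data and fits one of them. Both sample size justifications rest on percentages. A percentage has no mean and SD in the sense d needs, unless someone chooses a conversion. For variables the plan itself treats as non-normal, a mean/SD ratio is driven by the same tail values that led the plan to leave the t-test.

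The stake is interpretation. Because d is the stated criterion of clinical significance, the label a reader sees can depend on an undeclared conversion or on the measurement scale. For the sizing endpoint, the quantity the trial was designed around is a difference in percentage points, and the plan does not name it as the effect measure.

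**Working it through.** **1. The plan's own figure.** Inputs from the Sample size calculation section: "assuming an alpha risk of 0.05 and a beta risk of 0.2 in a bilateral contrast", rates 30% and 50%, "requires 110 subjects in the placebo group and 110 subjects in the Nutritional supplement group", and "including a 15% loss estimated". With pooled variance and no continuity correction:

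n = [1.96·√(2·0.4·0.6) + 0.842·√(0.3·0.7 + 0.5·0.5)]² / 0.20² = 93 per arm

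93 / (1 − 0.15) = 109.4, rounded up to 110 per arm. The stated figure reproduces.

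**2. The effect on the scale the trial is sized on**, at the planned rates with 93 evaluable per arm:

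- Risk difference = 0.50 − 0.30 = 0.20.
- SE = √(0.21/93 + 0.25/93) = 0.0703.
- 95% CI = 0.20 ± 1.96·0.0703, which is 6.2 to 33.8 percentage points.

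**3. Cohen's d for the same 30% against 50%:**

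| Conversion | Formula | d | Label in the plan |
|---|---|---|---|
| 0/1 coding | 0.20 / √((0.21 + 0.25)/2) | 0.417 | small |
| Logit | ln(2.333)·√3/π | 0.467 | small |
| Probit | Φ⁻¹(0.5) − Φ⁻¹(0.3) | 0.524 | none: between the 0.2–0.5 and 0.6–0.8 bands |

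Nor does d follow the 20-point difference. By the logit conversion, 5% against 25% gives 1.02 (large), while 40% against 60% gives 0.45 (small).

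**4. Non-normal variables.** The documents give no analyte distributions, so lognormal data are an assumption here. Hold the separation between arms at 0.50 SD on the log scale. The probability of superiority is then Φ(0.5/√2) = 0.638 whatever the skew. Raw-scale d is (m₁ − m₀)/√((v₀ + v₁)/2), with m = exp(μ + s²/2) and v = (exp(s²) − 1)·exp(2μ + s²):

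| Log-SD (s) | d on log scale | d on raw scale |
|---|---|---|
| 0.5 | 0.50 | 0.46 |
| 1.0 | 0.50 | 0.36 |
| 1.5 | 0.50 | 0.23 |

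The rank separation is the same in every row, and only the raw-scale d changes.

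**5. How often the label would turn to negligible.** This was simulated with a geometric mean ratio of 0.7, 93 per arm, one time point and 3,000 to 4,000 trials per setting. The table shows the share of trials with Mann-Whitney p < 0.05 in which raw-scale d is below 0.2:

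| Log-SD | Share labelled negligible |
|---|---|
| 0.5 | 0.05% or less |
| 0.7 | about 1.6% |
| 1.0 | about 12% |
| 1.5 | about 35% |

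Mean raw-scale d was 0.28 at log-SD 1.0 and 0.15 at 1.5. The log-scale values are ln(1/0.7)/1.0 = 0.36 and ln(1/0.7)/1.5 = 0.24.

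**The case against.** A reader might infer that the sizing endpoint will be reported as a Cohen's d, or that the trial's key results will carry no valid effect estimate. The document supports neither.

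- It never says d is computed on the percentage. Dichotomous variables have their own test and their own description, and a standardised mean difference is naturally read as meant for quantitative variables.
- Percentages per arm will be reported, so the difference can be obtained by subtraction and its interval by formula.
- For variables judged normal, possibly including the continuous EQ-5D-5L, d is a valid standardised effect.
- The lack of a stated confidence interval may be settled in a statistical analysis plan that is not shown, so it cannot carry the point.
- The skew figures depend on the assumed log-SD and nearly vanish at moderate skew. They also model one time point, whereas the plan concerns change from before to after treatment.
- A small d beside a significant rank test is not a contradiction, because the two answer different questions. The sign of d was reversed in only 0.2% (log-SD 1.0) to 4.8% (1.5) of significant simulated trials.

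All of this stands and limits the scope. It does not remove the mismatch. If d applies to percentages, its value is undefined until a conversion is chosen. If it does not, the plan's only criterion of clinical significance is absent for the endpoint that justifies the sample size. For rank-tested variables, the published rule pairs a mean-based measure with a median summary. An analysis plan would have to override that rule, not merely add detail.

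**Conclusion.** The point holds within limits and should be corrected. The plan fixes an effect measure that suits t-tested variables only. For percent improved, the value runs from 0.42 to 0.52 at the planned rates, and at the top of that range it falls in no labelled band. This part needs no assumption beyond the plan's own rates.

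For rank-tested variables the mismatch between measure, summary and test is certain, but its practical size is not. Under strong lognormal skew (log-SD 1.0 to 1.5, geometric mean ratio 0.7, 93 per arm), about 12% to 35% of significant results would be called negligible. At log-SD 0.7 or less the share is under 2%. Results for normally distributed variables, the choice of tests and the sample size are not affected.

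**What to change.** Replace the effect-size sentence with a measure matched to each test, always NG minus PG (or NG to PG for ratios):

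- **Percent improved and other dichotomous outcomes:** risk difference with 95% CI.
- **Variables tested by Mann-Whitney:** Hodges-Lehmann shift with 95% CI or, for laboratory analytes, the geometric mean ratio from log values with 95% CI.
- **Variables tested by t:** mean difference in scale units with 95% CI, with Cohen's d kept, if wanted, as a descriptive addition here only.

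Clinical significance should no longer be read from d for the first two groups.

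The cost is one paragraph of wording and a little more output. No new data or patients are needed, and 110 per arm stands. The one loss is that results no longer share a single unit-free scale.

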### Outcome measures

#### Primary outcome: Quality of life: EQ-5D-5L.

The EQ-5D-5L is a generic instrument for measuring health-related quality of life that has been validated [23] in Spanish and in PCC patients. It consists of two components: the levels of severity by dimensions and a visual analogue scale (VAS) on general health. The descriptive system contains five dimensions of health (mobility, self-care, activities of daily living, pain/discomfort, and anxiety/depression) and each of them has five levels of severity (From 1=No problem to 5=unable to perform). Participants indicate their perceived overall health on a VAS from 0 (“worst health I can imagine”) to 100 (“best health I can imagine”). The values obtained will be compared with the reference values [24]. Quality of life will be analyzed as a continuous variable by comparing the relevant statistics according to their distribution at the two points in time and as a qualitative variable by comparing the percentage of patients who improve their scores.

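### Cohen's d is named as the means of judging clinical significance, but it cannot show whether a gain matters to patients, and its bands leave unrounded values between 0.5 and 0.6 without a class (minor)

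*Protocol article*

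**What the plan says.** The Statistical analysis section of the protocol article gives d a specific job: "Effect size will be calculated using Cohen’s d to determine clinical significance". It then states that "negligible, small, medium and large differences will be reflected in effect sizes", with the limits given as "effect sizes of < 0.2, 0.2–0.5, 0.6–0.8 and > 0.8". It states no rounding rule for d, and it does not say which label counts as clinically relevant.

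Two other parts of the article bear on the meaning of a gain in the primary outcome:

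- The primary outcome section plans to analyse EQ-5D-5L as a continuous variable and also "as a qualitative variable by comparing the percentage of patients who improve their scores". It does not say how large an improvement must be. It also plans a comparison with reference values.
- The sample size section is built on the proportion improving, "expected to be 30% and 50%, respectively", in the placebo and supplement groups.

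**The concern.** **Purpose.** Clinical significance asks whether the difference is large enough to matter to patients. A standardised difference answers another question: how large the difference is compared with the spread of the sample. The same gain on the EQ-5D-5L can earn a different label in a more or a less homogeneous sample. If the report takes its relevance statement from these labels, that statement depends partly on who was recruited.

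**Bands.** The limits join at 0.2 and at 0.8, but not between the second and third bands. Taken literally, a d of 0.53 or 0.57 is neither small nor medium. The choice of label could then be made after the result is known.

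What is at stake is the interpretation of the result. The between-group comparisons themselves do not depend on d.

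**Working it through.** **1. Reproduce the plan's own figure, to obtain the number of completers.**

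Inputs from the sample size section: "assuming an alpha risk of 0.05 and a beta risk of 0.2 in a bilateral contrast"; rates of 30% and 50%; "including a 15% loss estimated". Allocation is 1:1 (Allocation and blinding).

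n per arm = [1.960 × √(2 × 0.40 × 0.60) + 0.842 × √(0.30 × 0.70 + 0.50 × 0.50)]² / 0.20² = 93 (no continuity correction).

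93 / (1 − 0.15) = 109.4, rounded up to 110. This matches the stated 110 per group, so 93 completers per arm is the figure the plan implies.

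**2. Read the bands.**

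| Value of d | Class as written |
|---|---|
| below 0.2 | negligible |
| 0.2 to 0.5 | small |
| above 0.5 and below 0.6 | none |
| 0.6 to 0.8 | medium |
| above 0.8 | large |

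If d is first rounded to one decimal, every value has exactly one class and the third row disappears.

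**3. How often an unrounded estimate would land in the gap.**

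Normal approximation, SE(d) = √(2/n + d²/(4n)) with n = 93. At d = 0.50: √(2/93 + 0.25/372) = 0.149. The chance is Φ((0.6 − d)/SE) − Φ((0.5 − d)/SE).

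| True d | Chance that the estimate lies between 0.5 and 0.6 |
|---|---|
| 0.30 | 7% |
| 0.40 | 16% |
| 0.50 | 25% |
| 0.55 | 26% |
| 0.60 | 25% |

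With one-decimal reporting, each of these becomes 0%.

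The gap lies in the range this trial can reach. With 93 per arm, the smallest d that reaches significance is about 1.960 × √(2/93) = 0.29, and the smallest detectable with 80% power is (1.960 + 0.842) × √(2/93) = 0.41. As a rough guide, suppose that improving means crossing one threshold on a normally distributed change score with equal SD in both arms. The design rates of 30% and 50% then correspond to d = z(0.50) − z(0.30) = 0.52. That model is an assumption; the article does not state it.

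**4. Dependence of the label on the SD.**

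d = raw difference / SD. The article gives no SD, so both the SDs and the raw differences below are assumed for illustration, on the 0 to 100 VAS.

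| Raw difference | SD 15 | SD 20 | SD 30 |
|---|---|---|---|
| 5 points | 0.33 | 0.25 | 0.17 |
| 8 points | 0.53 | 0.40 | 0.27 |
| 10 points | 0.67 | 0.50 | 0.33 |

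The same 10-point difference is medium at SD 15 and small at SD 30, whether or not d is rounded. Taken unrounded, a 5-point difference is small at SD 15 and negligible at SD 30, and an 8-point difference at SD 15 has no class. Closing the gap therefore does not remove this dependence.

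**5. Whether anything else in the article does the job.**

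The percentage improving has no stated size of improvement. The EQ-5D-5L reference values and the cut-offs for the fatigue, anxiety and depression scales describe a patient's status. None of them is a threshold for a meaningful difference between groups.

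**The case against.** The strongest reply is that this is a matter of wording. All four bands are written to one decimal, and at that precision they are exhaustive and do not overlap. The labels are descriptive, and the trial's comparisons use the t-test, Mann-Whitney or chi-square test. A value in the gap loses only an adjective, because d is still calculated and can be reported. A condensed article may also leave a minimal important difference to the full protocol or analysis plan.

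Much of this stands. The rounding reading is possible, so the 25% figure is conditional on unrounded d. The consequence is limited to interpretation. The last argument does not dispose of the point, however. The article does not simply leave the criterion of clinical significance unstated; it assigns that role to d, which cannot fill it.

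Three stronger readings are tempting, and the article does not support them:

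- *That d is a pass/fail test that could declare a trivial gain relevant.* No label is named as the threshold for relevance, so no such test exists in the text.
- *That d replaces medians or rank-based results for non-normal variables.* The section plans medians and rank tests for such data and also plans d, but it does not say that d is the only effect measure there. A rank-based effect size would be a sensible addition, but its absence is not an error.
- *That the trial will fail to classify its result one time in four.* This requires both unrounded d and a true d of about 0.5 to 0.6.

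**Conclusion.** The point holds and is minor. The more important part needs no assumption about the data: a measure scaled by the sample SD is the only stated means of judging clinical significance, and it cannot show whether an EQ-5D-5L difference matters to patients. The gap in the bands is real as written, but it depends on d being classified unrounded. On that basis, with 93 completers per arm and a normal approximation, about 25% of estimates fall in it if the true d is 0.5 to 0.6, 16% if it is 0.4 and 7% if it is 0.3.

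A reader might infer that the primary analysis is compromised. It is not: the primary test, the type I error and the 110 per group are the same with or without this rule. What changes is what the report can properly say about clinical relevance.

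**What to change.** Amend the Statistical analysis section before unblinding:

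1. Make the bands contiguous and non-overlapping, for example below 0.2, 0.2 to <0.5, 0.5 to <0.8, and 0.8 or more. This moves exactly 0.5 from small to medium and exactly 0.8 from medium to large. Another allocation of the boundary values would also serve, provided it is fixed in advance.
2. Describe d as a descriptive effect size only, and remove its role in determining clinical significance.
3. Judge clinical significance on the raw between-group difference in EQ-5D-5L, with its 95% CI, against a minimal important difference. That difference should be named with its source, on the same score, before unblinding.
4. Optionally, report a rank-based effect, such as a median shift or probability of superiority, for variables compared by rank tests.

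The cost is a few sentences of analysis text, with no new data and no change to the sample size. The one real downside for the sponsor is that the relevance statement may turn out less favourable than a size label would have been.
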